### Plans for collection, laboratory evaluation, and storage of biological specimens for genetic or molecular analysis in this trial/future use {33}

See the “ Additional consent provisions for collection and use of participant data and biological specimens {26b}” section; there will be no biological specimens collected, but the authors can tick a box on the informed consent form for the consent for the use of date for ancillary studies.

## Statistical methods

### Statistical methods for primary and secondary outcomes {20a}

Data for the primary outcome measure will be reported descriptively. Descriptive analysis will be performed in order to report outcome measures for the total population. Continuous data will be analyzed using an independent *t*-test or Mann–Whitney *U* test if not normally distributed. For continuous data, the mean and SD (parametric data) or the median and percentiles (non-parametric data) will be reported. For categorical data, numbers and frequencies will be reported. First, data will be reported for the entire study population. A subgroup analysis will be performed, discriminating between CR or withholding from CR. Differences in outcomes will be analyzed using the unpaired *T*-test in case of normally distributed data or the Mann–Whitney test in case of not normally distributed data. Separate analysis will be performed for average VAS score per patient and average VAS score per day to show both the overall average pain preoperatively and the daily trend towards day of surgery. This will show insight to possible effects on the average caused by patients waiting longer for their surgery. Descriptive analysis will be performed in order to report outcome measures for the total population (main analysis) and (if applicable) the subgroups as mentioned above. For continuous data, the mean and SD (parametric data) or the median and percentiles (non-parametric data) will be reported. For categorical data, numbers and frequencies will be reported. Given the expected low sample size, neither univariate nor multivariable analyses will be done. Trends in PRWE scores will be assessed using generalized linear mixed models calculating the marginal mean differences. Differences in complication rates and re-interventions will be analyzed using the chi-square test of Fisher’s exact test.

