**Discussion:**

If our study shows that patients who did not receive closed reduction experience no significant drawbacks, we might be able to reorganize the initial care for distal radial fractures in the emergency department. If surgery is warranted, the patient can be sent home with a plaster cast to await the call for admission, decreasing the time spend in the emergency room drastically.

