### Trial design {8}

This trial is designed as a non-inferiority multicenter cluster randomized trial. Participants will be equally distributed between the two treatment arms.

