### Sample size {14}

The sample size calculation is based on our primary outcome parameter: the VAS score for pain reported on a daily basis from the visit to the ED until the day of surgery. To find out if the pre-operative pain scores of patients that are refrained from CR are comparable with the scores of the CR group, we will use a non-inferiority test. This requires a non-inferiority margin, which is the biggest difference between the two groups in favor of the CR group, without a statistical difference [28]. The European Medicines Agency advices to base the non-inferiority margin on a difference that is not clinically important [29]. Therefore, our non-inferiority margin is 50% of the minimal clinical important difference (MCID) of the VAS [28]. Based on a systematic review concerning the MCID of VAS scores, a MCID is a context-specific and methodological dependent value [30]. To the best of our knowledge, the MCID of the VAS score for DRFs is unknown. Therefore, we used the MCID of a study that included trauma patients with isolated acute extremity pain [31]. For the description of the MCID of the VAS score, the VAS scale is seen as a 100 mm line. With an MCID of 19.3 mm, our non-inferiority margin will be 9.7 mm (= 50%). As only Bird et al. provide a standard deviation (SD) around the MCID, we will use that value of 15 mm for our sample size calculation [24]. To correct for a cluster-effect we use an intra-cluster correlation (ICC) coefficient between the different hospitals of 0.06, which is generally reported in the literature for hospital processes. To calculate the required sample size, two simulations were run both assuming a fixed number of six clusters (hospitals). In the first simulation, an equal number of subjects per hospital was assumed. Hospitals were randomized to start with treatment A (3 centers) or B (3 centers) in a 1:1 fashion and crossed over after half of the patients were included. For total sample sizes varying from 12 to 502 with increments of 12, 5000 simulations were run for each sample size considered. In each simulation, random data was generated under the specifications described above. A linear mixed model was fitted with a random intercept for cluster and treatment group as fixed effect. A 95% confidence interval was calculated based on the t-distribution with degrees of freedom estimated by the Satterthwaite method. The power was calculated as the percentage of simulations in which the upper limit of the 95% confidence interval was smaller than the non-inferiority margin. From the first simulation, it followed that, using a two-sided alpha of 5%, *n* = 80 patients total would be required in total to demonstrate non-inferiority with a power of 80% (Fig. 1).

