
**Fig. 1 Fig1:**
[figure not shown]
Power curve for simulation 1 assuming of balanced clusters (equal number of patients included per center)

However, in practice, unequal number of patients is expected to be included by each center. Also, seasonal effects should be accounted for in the analysis. Therefore, a second simulation was conducted in a similar way. The number of patients included per center was (roughly) based on the number of eligible patients in the past year (known for 4 hospitals) divided by 2 (assuming that 50% of eligible patients would participate). Inclusion rates for the two hospitals for which this was not known were set equal to the hospital with lowest inclusion rate, resulting in monthly inclusions of 13, 7, 7, 1, 1, 1. Seasonal effects were included by a monthly effect, which were assumed to follow a sine function with a period of 12 months. The SD of the seasonal effects over a 12-month period was set equal to the between cluster SD. The half period (*x* = *π*) was set equal to the moment of cross-over. For sample sizes varying from 60 (two months of inclusion) to 360 (12 months of inclusion), again 5000 simulations were run for each sample size considered. Linear mixed models were fitted including center as random effect and month and treatment as fixed effects. Using a two-sided alpha of 5%, *n* = 120 patients total (rounded to above) would be required in total to demonstrate non-inferiority with a power of 80% (Fig. 2). Accounting for a 10% loss to follow-up, a total of *n* = 134 patients will be included. It should be noted that in the simulations, it was assumed that only one VAS pain will be collected for each patient, while in reality multiple VAS scores (one per day) will be obtained during the period between the visit to the emergency department and the operation. An average VAS pain for each patient will be estimated by a multilevel linear mixed model using random intercept for patient nested within center. Including this aspect in the simulation studies was deemed too complicated, since no reliable estimates for the correlation between daily VAS pain scores in this setting are available. However, following the reasoning that multiple measures will lead to a more precise estimate than a single measure, it can be expected that in practice a higher power will be achieved compared to the simulations and including this is not strictly necessary (i.e., the simulations can be regarded as conservative in this respect).

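### The arm comparison stated in {20a} contradicts the non-inferiority test and mixed model on which the sample size rests, so the primary analysis must be stated once

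*Protocol article*

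**What the plan says.** **Design and sizing.** Trial design {8} states: "This trial is designed as a non-inferiority multicenter cluster randomized trial". Sample size {14} says of the primary outcome that "we will use a non-inferiority test", sets the margin at 9.7 mm, and counts a simulated trial as a success when the upper 95% confidence limit lies below the margin. It says that season should be allowed for in the analysis. For the simulation behind the final number it reports: "Linear mixed models were fitted including center as random effect and month and treatment as fixed effects".

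**Analysis.** Statistical methods {20a} says the primary outcome will be reported descriptively, and then: "A subgroup analysis will be performed, discriminating between CR or withholding from CR". The arms are to be compared by an unpaired t-"test in case of normally distributed data or the Mann–Whitney test in case of not normally distributed data". It adds: "Given the expected low sample size, neither univariate nor multivariable analyses will be done". For this comparison it gives no margin, confidence interval, center or month.

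**Mixed models elsewhere.** Sample size {14} uses a multilevel model to estimate each patient's average VAS, section {20c} uses a linear mixed model for missing data, and {20a} uses generalized linear mixed models for PRWE trends. None of these defines the treatment contrast that is to be set against 9.7 mm. Outcome assessment {18a} calculates the patient's average differently, as the sum of the scores divided by the number of days.

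**The concern.** The trial was sized for one test and its analysis section describes another. A t-test or Mann–Whitney test asks whether the arms differ. Failing to find a difference is not evidence that the harm is smaller than 9.7 mm, and it becomes easier as the data become noisier. Mann–Whitney gives no mean difference in mm to set against the margin.

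Hospitals are the randomised units and switch arm halfway, and the plan expects very unequal recruitment. Arm, hospital and calendar time can therefore be partly confounded in any one allocation. That is why the sizing model contains center and month, and the {20a} comparison contains neither.

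At stake is the main conclusion. In an open-label trial with several competing analysis statements, the choice between them should not be left until the data are seen.

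**Working it through.** **1. The plan's own figures.** Inputs from Sample size {14}: margin 9.7 mm, SD 15 mm, two-sided alpha 5%, power 80%.
- Normal formula: n per arm = 2 × (1.960 + 0.842)² × 15² / 9.7² = 37.5, so 38 per arm or 76 in total. With the t-distribution, power is 79.4% at 76, 80.5% at 78 and 81.5% at 80. This agrees with the stated 80.
- Second simulation, rebuilt with 13, 7, 7, 1, 1, 1 inclusions per month, ICC 0.06 and seasonal SD equal to the between-hospital SD: a center-plus-month model has power of about 78% at 90 patients and 89% at 120. So 120 is the first whole-month step above 80%.
- Dropout: 120 / 0.9 = 133.3, so 134.

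The sample size is sound for the model-based interval test.

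**2. Difference test against non-inferiority rule.** Independent data, SD 15, 60 per arm. A two-sided 5% level is assumed for the t-test, because {20a} does not state one.
- SE = 15 × √(2/60) = 2.739 mm; t quantile (118 df) = 1.980; half-width = 1.980 × 2.739 = 5.42 mm.
- The t-test is non-significant for an observed difference up to 5.42 mm.
- Non-inferiority needs an observed difference below 9.7 − 5.42 = 4.28 mm.

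An observed 4.3 to 5.4 mm against no CR would read as no difference and yet fail non-inferiority.

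**3. Probability of a non-significant t-test when the true difference is 9.7 mm** (noncentral t):

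| SD (mm) | 60 per arm | 67 per arm |
|---|---|---|
| 15 (plan) | 6.0% | 4.0% |
| 20 (assumed) | 25.0% | 20.4% |
| 25 (assumed) | 44.1% | 39.4% |

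The reference is the 2.5% one-sided error of the sizing rule. SDs of 20 and 25 are not in the document; they show the direction of the effect.

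**4. A t-based 95% interval set against 9.7 mm.** Simulation at a true difference of 9.7 mm, N = 120 over 4 months, cross-over at month 2, all 20 ways of starting three hospitals on each arm. ICC 0.06 gives a between-hospital SD of 15 × √0.06 = 3.67 mm, and the sine has the same SD. The text gives both a 12-month period and a half period at the cross-over, so both readings were run. Center was fitted as a fixed effect, as an approximation to the random effect.

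| Recruitment | Season | t interval | Center + month |
|---|---|---|---|
| 13/7/7/1/1/1 | none | 2.3% | 2.5% |
| 13/7/7/1/1/1 | 12-month sine | 5.4% | 2.5% |
| 13/7/7/1/1/1 | one cycle over the trial | 8.5% | 2.4% |
| equal | none | 2.2% | 2.5% |
| equal | 12-month sine | 2.0% | 2.5% |
| equal | one cycle over the trial | 1.9% | 2.5% |

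Other runs with season and unequal centers, with the sine handled differently or recruitment spread over 10 months, gave roughly 3% to 9%. With unequal centers and season over 4 months, the t interval's error is 3.6–4.5% at ICC 0.02 and 7.4–12.6% at ICC 0.10.

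**The case against.** The strongest reply is that {20a} is not the only place to look. The sample size section commits in the future tense to a non-inferiority test and a margin, asks for season to be handled in the analysis, and plans a multilevel model for the patient average; {20c} adds a mixed model for missing data. The margin need not be repeated in {20a}, and a fuller analysis plan may exist. This stands to the extent that the fault is a contradiction, not proof that the wrong test will be run. It does not remove the fault: {20a} affirmatively states a different comparison, and none of the other mixed models supplies the treatment contrast.

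Four stronger readings are tempting and are not supported:
- **That the plan excludes all modelling.** It does not. The bar sits beside planned mixed models for PRWE, the patient average and missing data.
- **That the pooled population is the confirmatory analysis.** The main-analysis label in {20a} qualifies descriptive reporting.
- **That the abstract sets the decision rule.** Its phrase "patients who did not receive closed reduction experience no significant drawbacks" is conditional prose about implications.
- **That a t-test can never address the margin.** A t-based interval could be set against 9.7 mm if the plan said so. The impossibility holds only for Mann–Whitney.

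It is also fair that the error inflation in step 4 needs both season and unequal centers. Both are the plan's own simulation assumptions, but they are assumptions.

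**Conclusion.** The concern holds as an internal contradiction about the primary analysis. The comparison described in {20a} is not the test that produced 120 and 134 patients, and no other passage states the treatment contrast against the margin.

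At the plan's SD of 15 mm, reading a non-significant t-test as success would accept a true harm equal to the margin in about 4–6% of trials instead of 2.5%, rising to 20–44% if the SD were 20–25 mm (an assumption). These figures treat patients as independent and the t-test as two-sided at 5%.

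For a t-based interval set against 9.7 mm, the error of about 3–9% rests on ICC 0.06, a seasonal SD equal to the hospital SD and the 13/7/7/1/1/1 split. It falls to about 2% without season or with equal centers. The need for correction does not depend on that inflation, because the passages conflict whatever the season does.

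**What to change.** In {20a}, state one primary analysis: the treatment contrast, no CR minus CR, from the model used for sizing (random center, fixed month and treatment). Declare non-inferiority only if the upper limit of the two-sided 95% confidence interval is below 9.7 mm.

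For the primary outcome, remove the subgroup label, the t-test and Mann–Whitney options, and the bar on multivariable analysis.

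Reconcile the patient's average VAS: choose between the model-based estimate in {14} and the simple mean over days in {18a}, and say how daily scores enter the primary model. The two can weight patients differently when waiting times to surgery differ.

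The cost is small: a wording change with no change to the sample size or data collection, plus some model specification. That last part is new work if daily scores are modelled directly, because the simulations used a single VAS score per patient.

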## Introduction

### Background and rationale {6a}

Each year, almost 26,000 adults are treated for a displaced distal radius fracture (DRF) in the Netherlands, making it one of the most common fractures in the ED [1–4]. According to a Swedish study, approximately 60% (= 16,000) of all DRFs are displaced [5]. The majority of all displaced DRFs are treated with osteosynthesis. This surgery is semi-acute planned operative care, mostly within the first week after trauma.

The Dutch DRF guidelines advise to perform closed reduction (CR) of displaced DRFs awaiting surgery at the ED, because it may lead to post-reduction pain relief, and a successful reduction may warrant conservative treatment [6]. Techniques used for CR of DRFs are manual traction and finger-trap traction [7]. Both procedures are often painful despite injection of a local anesthetic between the fracture fragments [8–10]. Sometimes, the patient is even sedated (as well). Besides the physical discomfort associated with CR, patients may experience CR as a traumatizing event as well. This questions how relevant CR at the emergency department really is. The same guideline also acknowledges that evidence supporting the advice to perform a CR is lacking [11, 12]. Meanwhile, CR is a painful, costly, time-consuming procedure, often requiring anesthesia and most surgeons experience a substantial re-dislocation at surgery.

Furthermore, the guideline suggests that good fracture alignment justifies conservative treatment. This recommendation is based on three rather outdated randomized studies comparing cast immobilization with either external fixation of the wrist or percutaneous pin fixation [13–15]. However, both surgical techniques have been largely replaced by internal plate fixation. Recent European randomized controlled trials have shown that in displaced DRFs, despite acceptable fracture reduction, volar plating is superior to cast immobilization in terms of functional outcome, quality of life, and prevention of secondary dislocation [16–18]. This was also concluded in a large meta-analysis of 23 trials including 2254 patients, published last year [19]. Opposed to the current but rather old guideline, strong recent evidence suggests that operative treatment is preferred over conservative treatment in adult patients with displaced DRFs. A trend towards more operative treatments is expected and makes our research question more relevant.

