### Outcomes {12}

The primary outcome is the average of the pre-operative visual analog scale for pain (VAS) score, reported on a daily basis from the ED visit until surgery.

Secondary outcomes are wrist function measured with the Patient-Rated Wrist Evaluation (PRWE) score after 6 weeks and 3, 6, and 12 months, length of stay in the ED, type and quantity of used pain medication, patient satisfaction, quality of life, and complications. Furthermore, a cost-effectiveness analysis will be performed using the Medical Consumption Questionnaire (iMCQ) and Productivity Cost Questionnaire (iPCQ) [26, 27], and the ability to assess CT scans of unreduced fractures and reduced fractures will be compared.

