### Participant timeline {13}

The participant timeline is shown in Table 1.

**Table 1 Tab1:** Overview questionnaires

Name	Follow-up moment	Time spent per visit (minutes)	Time spent in total (minutes)
Listen, read and complete informed consent	ED	15	15
Pain diary	Every day until surgery	5	5 × 7–14* = 35–70
PRWE	6 weeks, 3 months, 6 months, 12 months	5	20
EQ-5D-5L	6 weeks, 3 months, 6 months, 12 months	5	20
ROM + grip strength	6 weeks, 3 months	1	2
Report used health resourced	6 weeks, 3 months, 6 months, 12 months	2	8
Report pain medication	6 weeks, 3 months, 6 months, 12 months	2	8
		**Total**	110–145

*Surgery usually takes place between 7 and 14 days

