## Data collection and management

### Plans for assessment and collection of outcomes {18a}

The primary outcome is the average of the pre-operative visual analog scale for pain (VAS) score, reported on daily basis from the ED visit until operation. The VAS score is an easy, valid, and reliable tool for pain measurement that has been widely used [32]. The VAS score will be presented as a horizontal line with in which the complete left side is defined as “no pain,” and the complete right side is defined as “the most extreme pain possible.” The patients will be asked to mark the position that corresponds with their pain experience. The VAS score prior and after the plaster application will represent their current pain experience. During the ED visit, patients will receive a “pain diary,” containing multiple empty VAS forms. Patients will be asked to report their average VAS score at the end of every day as well as the worst pain of that day (the latter will be used for a secondary analysis). The average will be calculated by adding all pain scores and dividing by the number of days for each patient. Besides the pre-operative VAS scores, they will also register the post-operative VAS score at 6 weeks and at 3, 6, and 12 months. The following parameters will serve as secondary outcome measures.

Average pain per day, average highest pain, and highest pain per day will all be analyzed to identify possible patterns secondary to the primary outcome of average pain from day 1 until surgery. The post-operative Patient-Rated Wrist Evaluation (PRWE) score [33] after 6 weeks and 3, 6, and 12 months will be assessed. The PRWE is a 15-item questionnaire designed to measure wrist pain and disability in activities of daily living. The PRWE allows patients to rate their levels of wrist pain and disability from 0 to 10 and consists of 2 subscales:Pain subscale: contains 5 items each of which is further rated from 1 to 10. The maximum score in this section is 50 and minimum 0Function subscale: contains total 10 items which are further divided into 2 sections, i.e., specific activities (having 6 items) and usual activities (having 4 items). The maximum score in this section is 50 and minimum 0

The length of stay in the ED will be measured in minutes and concerns the entire time that a patient is present in the ED. This will be calculated by subtracting the registration time from the discharge time.

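### The pooled daily pain mean runs over a changing set of patients, so by itself it cannot separate change over time from change in who still contributes

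*Protocol article*

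**What the plan says.** The primary outcome is each patient's average pre-operative VAS, "reported on a daily basis from the ED visit until surgery" (Outcomes {12}). Plans for assessment {18a} defines it arithmetically: "The average will be calculated by adding all pain scores and dividing by the number of days for each patient". Diary length therefore varies with time to surgery.

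Statistical methods {20a} adds a separate analysis of the "average VAS score per day to show both the overall average pain preoperatively and the daily trend towards day of surgery", and gives it a purpose: "This will show insight to possible effects on the average caused by patients waiting longer for their surgery". For continuous data that section names means or medians with a t-test or Mann–Whitney test. It also says "Given the expected low sample size, neither univariate nor multivariable analyses will be done", although its next sentence plans generalized linear mixed models for PRWE trends.

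Two other places mention a mixed model. Sample size {14} says "An average VAS pain for each patient will be estimated by a multilevel linear mixed model using random intercept for patient nested within center"; no term for day is named. Section {20c} names a linear mixed model for missing data. Neither is tied to the daily trend.

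On time to surgery, the Table 1 footnote says "Surgery usually takes place between 7 and 14 days", while Background {6a} says "mostly within the first week after trauma".

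**The concern.** A mean for a given diary day can include only patients who have a diary entry on that day. Once operations begin, the group shrinks and those left may differ from those who have gone, for example by hospital, fracture severity or scheduling priority. The resulting curve would then combine two things: how pain changes within a patient, and how the mix of patients changes. The text describes nothing that separates them: no waiting-time groups, no common set of days, no model with a day term.

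The article uses this output to judge whether longer waits affect the average. A trend created or masked by composition could wrongly reassure or alarm readers about the effect of waiting, and daily means late in the series would rest on few patients.

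**Working it through.** The plan gives no figure for the daily trend, so there is none to reproduce. Its sample size is used for the counts below: 120 / 0.9 = 133.3, rounded up to the stated 134.

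**Inputs from the article:** SD 15 mm, margin 9.7 mm, 134 patients, waits usually 7 to 14 days (Table 1 footnote).

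**Assumptions, not in the article:**
- Waits are uniform on 7, 8, …, 14 days.
- Days are counted from the ED visit, and a patient contributes on day d if the wait is at least d.
- Pain is flat within every patient.
- The correlation r between wait and pain level is 0, ±0.15 or ±0.3.
- The between-patient SD is either 15 mm (all the variation lies between patients) or 12 mm (with 9 mm daily variation, √(12² + 9²) = 15).

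**Coverage.** The share contributing on day d, for d from 7 to 14, is (15 − d)/8:
- day 7: 100%
- day 8: 87.5%
- day 10: 62.5%
- day 12: 37.5%
- day 14: 12.5%, or 134 × 0.125 ≈ 17 patients, about 8 per arm

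**Drift.** The wait has mean 10.5 and SD √((8² − 1)/12) = √5.25 = 2.291. Among those still contributing on day d the mean wait is (d + 14)/2. The pooled mean therefore moves by

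drift(d) = r × SD × [(d + 14)/2 − 10.5] / 2.291.

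On day 14 the bracket is 3.5, and 3.5/2.291 = 1.528:

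| r | between-patient SD 12 mm | between-patient SD 15 mm |
|---|---|---|
| 0 | 0 | 0 |
| ±0.15 | ±2.7 mm | ±3.4 mm |
| ±0.3 | ±5.5 mm | ±6.9 mm |

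At r = 0.3 and SD 15 mm the drift is 4.5 × 1.5/2.291 = 2.9 mm on day 10 and 4.5 × 2.5/2.291 = 4.9 mm on day 12. No patient's pain changes in this example, so all of the movement comes from composition.

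**Earlier departures.** With waits uniform on 3 to 14 days, 8/12 = 67% still contribute on the seventh diary day. The wait SD is √((12² − 1)/12) = 3.452, the mean wait of those left is 10.5 against 8.5 overall, and at r = 0.3 with SD 12 mm the drift is already 0.3 × 12 × 2/3.452 = 2.1 mm.

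**When wait and pain are unrelated.** The daily mean is unbiased for the time trend. Suppose pain starts at 50 mm and falls by 2 mm a day. The curve recovers that fall, and it explains why the per-patient average is 50 − 2 × 3 = 44 mm for a 7-day wait and 50 − 2 × 6.5 = 37 mm for a 14-day wait.

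**Does a model with a day term help?** In simulated trials of 134 patients with flat pain (between-patient SD 12 mm, daily SD 9 mm, 60 trials per setting), the raw day-14 minus day-1 difference averaged −5.0 mm at r = −0.3 and +5.6 mm at r = +0.3. A random-intercept model with day as a fixed effect gave 0.1 and 0.6 mm.

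**The case against.** Several points against the concern carry weight.

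- **Day scale.** The wording about the trend towards surgery may mean days counted back from surgery. With waits of 7 to 14 days everyone would then contribute to the last seven days, and the composition would change only at the early end. This stands: it moves the problem without removing it, and the article does not say which scale is meant.
- **Start at day 7.** A reader might infer that distortion begins on day 7. That rests on a footnote that says usually, and it conflicts with Background {6a}. Under the footnote taken literally, coverage is still complete on day 7. Under the Background statement, departures begin earlier.
- **No possible insight.** A reader might infer that the daily mean can tell us nothing about longer waits. That is too strong. Days on which all patients contribute are unaffected, and if wait and pain are unrelated the curve does show how later days enter a longer-waiting patient's average.
- **Modelling excluded.** A reader might take the sentence on univariate and multivariable analyses as a ban on modelling. The article plans mixed models in three places; the gap is that none is tied to this trend.
- **Bias between arms.** A reader might infer that the arms would be distorted differently. Nothing in the documents shows this. With the same wait-pain link in both arms at r = 0.3, a simulated day-14 arm difference was 0.03 mm. Each hospital also crosses over, so hospital scheduling acts on both arms.
- **Size.** The correlation is assumed. The drift is a change over time in a pooled mean, whereas 9.7 mm is a between-arm margin for the primary average, so the margin gives only a sense of scale.
- **Detail for the analysis plan.** Denominators and model terms are often left to that document, which is not shown. But the article itself states both the method and the conclusion to be drawn from it, and the point concerns that pairing.

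**Conclusion.** The point holds in a limited form. That the contributing patients change from day to day follows directly from a diary that ends at surgery. Whether this distorts the daily mean depends on a relation between wait and pain that the documents do not quantify. Under the stated assumptions the drift by day 14 is 0 if there is no relation and about 5.5–6.9 mm at a correlation of ±0.3. The planned summary cannot by itself tell within-patient change from a change in who is left, so it does not on its own support the insight claimed for it.

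This is a secondary analysis. The non-inferiority test on the per-patient average is not directly affected. The change is worth making because it is cheap, not because the trial's main conclusion is at risk.

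**What to change.** 1. State the day scale: days since the ED visit or days before surgery.
2. Estimate the daily trend with the multilevel model already named in Sample size {14} (patient nested within center), adding fixed effects for day, arm and day-by-arm.
3. Report the number of patients contributing per arm on each day.
4. Limit daily arm comparisons to days on which nearly all patients are observed to contribute. Set this from observed coverage and not as a fixed window of days 1 to 7.
5. Reconcile Background {6a} and the Table 1 footnote on time to surgery.
6. To address longer waits, show mean pain curves by waiting-time group in addition to the model. A random intercept handles differences in pain level between short and long waiters, but it would not reveal a different slope; the grouped curves would.

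The cost is a change of analysis wording, with no new data. The downside is that no arm comparison is reported for the sparse days.
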